**Table 2 Intervention conditions according to TiDieR criteria (Continued)**

|                                                                                                                                                                                            |                                                                                                                                                                                                                                                                                                                                                                                                                                                                            |                                                                                                                                                                                                                                                                                                                                                                                                                                                                            |
|--------------------------------------------------------------------------------------------------------------------------------------------------------------------------------------------|----------------------------------------------------------------------------------------------------------------------------------------------------------------------------------------------------------------------------------------------------------------------------------------------------------------------------------------------------------------------------------------------------------------------------------------------------------------------------|----------------------------------------------------------------------------------------------------------------------------------------------------------------------------------------------------------------------------------------------------------------------------------------------------------------------------------------------------------------------------------------------------------------------------------------------------------------------------|
| describe the changes (what, why, when, and how)                                                                                                                                            |                                                                                                                                                                                                                                                                                                                                                                                                                                                                            |                                                                                                                                                                                                                                                                                                                                                                                                                                                                            |
| Item 11. How well (planned)?: if intervention adherence or fidelity was assessed, describe how and by whom, and if any strategies were used to maintain or improve fidelity, describe them | Research assistants will be present daily on study wards to both promote and monitor intervention fidelity in terms of which wards should be receiving weekend allied health services and which should not. Patient contact statistics are recorded by allied health professionals and are recorded in hospital administrative datasets. These datasets will be used by investigators to measure time spent by weekend allied health personnel with patients on each ward. | Research assistants will be present daily on study wards to both promote and monitor intervention fidelity in terms of which wards should be receiving weekend allied health services and which should not. Patient contact statistics are recorded by allied health professionals and are recorded in hospital administrative datasets. These datasets will be used by investigators to measure time spent by weekend allied health personnel with patients on each ward. |
| Item 12. How well (actual)?: If intervention adherence or fidelity was assessed, describe the extent to which the intervention was delivered as planned                                    | Not applicable for protocol                                                                                                                                                                                                                                                                                                                                                                                                                                                | Not applicable for protocol                                                                                                                                                                                                                                                                                                                                                                                                                                                |

approach being used in this study [21]. Patients who meet one of these criteria will be permitted to see a weekend allied health staff member despite them being on a ward during a ‘control’ period. Local nursing or medical staff will identify if the patient meets the pre-determined set of criteria, which allows for them to be seen by an allied health professional over a weekend. This will be escalated to the site allied health director or project site liaison who will approve provision of the service following a final check against the ‘clinical exception’ criteria. These criteria will be suggested by ward-

level staff during pre-trial group interviews, and managers through key-informant and group interviews and will vary from site to site. Staff will be asked to provide evidence to support their request for a clinical exception criteria (for example, research papers, local incident reports, hospital policy), and project investigators will determine whether the strength of evidence presented warrants formation of a clinical exception criterion. The frequency of clinical exceptions under each criterion will be recorded to monitor control condition fidelity. Project data collectors at each site will be present on

[figure not shown]

each ward each day of this project and will facilitate on-going communication with ward staff regarding local clinical exception criteria.

### **Study 2 - control condition - no weekend allied health services**

This will be identical to the study 1 control condition.

### **Study 2 - intervention condition - stakeholder-driven model of weekend allied health services**

A criticism of using the current model of weekend allied health service provision as the intervention in study 1 is that it is possible that the sites involved may have constructed their prevailing model on an *ad hoc* basis, which may not reflect higher standards of service set in other hospitals. This is consistent with evidence already discussed that there is high variability in the amount and focus of allied health services already being delivered on weekends internationally [1]. However, there is no existent 'gold standard' for how a weekend allied health service delivery model should be structured (which services, how much, what activities) given the paucity of evidence regarding the comparative efficacy of different weekend allied health service delivery models. Developing such a standard across all medical and surgical wards may also be an impossibility, as different types of wards will have different patient casemix and different allied health service requirements.

Rather than conform to a non-existent 'standard' for what a weekend allied health service delivery model should look like, we have sought to standardise a process by which an 'optimal' site-specific service could be developed. Thus, the model of allied health service delivery used as the intervention in study 2 of this research is a complex intervention [24].

Our process for developing this site-specific weekend allied health service delivery model begins with extensive consultation with relevant stakeholders (medical, nursing and allied health staff and managers) on participating wards. These staff will be interviewed (group and individual, key informant) to drive development of this model; hence, we refer to this model as a stakeholder-driven model. Investigators experienced in conducting qualitative and participatory action research (LO, FM) will facilitate these interviews. These staff will not be asked to say which professional discipline they want to be employed on the weekends, rather, to identify and prioritise the tasks that they believe to be most important for allied health to perform on weekends both in terms of improving patient health outcomes, improving patient flow, and reducing readmissions. They will also be asked to reflect on the strengths and limitations of the current model of care, suggest areas for improvement and to examine patient incident and clinical

exception data gathered during the first study of the trial to inform their decisions. Allied health managers will be provided with this list of tasks and other feedback gathered, so that they can propose what the new, stakeholder-driven model of weekend allied health service delivery will be. Transdisciplinary, interdisciplinary and multidisciplinary models of care are all possible candidates for the model of care that will arise from this process. These managers will then be engaged in a Delphi process [25] to select the preferred model of care from the proposals generated.

Each site will hold constant the budgetary amount allocated to weekend allied health services between studies 1 and 2. During the second 'step' in the stepped wedge design of study 2, the first ward to resume provision of weekend allied health services using the stakeholder-driven model will be provided with a budgetary allocation that is the average per ward of study 1. During the third step, when a second ward resumes provision of weekend allied health services, the total budgetary allocation to be shared between the 2 wards that have resumed provision of the weekend service will be twice the average per ward of study 1. However, provisions within the stakeholder-driven model will be made to allow weekend allied health to distribute their time unequally between the two wards based on the task prioritisation framework provided to them by the stakeholders who designed this model. This provision recognises that an optimal service would target patients who are likely to receive the greatest benefit from this service, regardless of the ward they are physically being treated on.

### **Outcome measures**

Current United Kingdom Medical Research Council guidance on the evaluation of complex interventions indicates that a single primary outcome may not make best use of data in these evaluations, rather, that a range of outcome measures will be needed including possible unintended consequences [23]. In this research, we plan to examine three domains of primary outcome with one domain being analysed in two ways, and another being measured as a composite outcome.

#### **Primary outcome measure: 1) length of stay**

Mean overall length of stay per patient who is treated on one of the targeted wards will be used as the primary outcome. This measure is often used as an indicator of hospital efficiency [26]. Length of stay is the key overall driver of inpatient costs and is the most readily available outcome to enable stopping rules to be checked during study 1. However, overall mean length of stay is limited as an outcome for this project as: i) these data can be skewed by highly influential outliers, ii) length of stay of longer-stay patients will not be known until they are

discharged (thus interim analyses for non-inferiority to check stopping rules may underestimate mean length of stay) and iii) patient admission casemix profile may vary over the study period (for example, a study ward may start admitting more patients who typically stay longer). To account for these limitations, we will also examine the proportion of patients who stay longer than their Australian Refined Diagnosis-Related Group average 'in-liner' length of stay according to data published from the previous year [27].

**Primary outcome measure: 2) rate of unplanned hospital readmission within 28 days**

This routinely collected measure will be used as a marker of treatment effectiveness, discharge planning and patient readiness for discharge [28].

**Primary outcome measure: 3) rate of adverse events**

Patient adverse events will be collected using a range of clinical data collection systems. The events quantified will be in-hospital falls, Code Blue/Medical Emergency Team calls, pulmonary embolus, deep vein thrombosis, death, hospital acquired pressure area, and intensive care unit admission from the ward. Rate of adverse events (events per person-time) will be considered as a single, composite end-point when considered as a primary outcome. A composite end point for this primary outcome domain was selected as a number of different clinical events may indicate a clinical failure, whereas the selection of only one type of clinical event as the end point may not present a comprehensive clinical picture [29].

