### **Trial safety**

The process of disinvestment in allied health services has the potential to be detrimental to patient safety and/or organisational outcomes. The checking of stopping rules and development of clinical exceptions will, therefore, be used to ensure safety. A stopping rule allows data to be monitored and the trial to be stopped if there is evidence of a lack of safety or efficacy associated with the intervention [34]. During study 1, interim analyses will be conducted monthly to ensure that patient outcomes have not dropped below a pre-specified non-inferiority margin. This margin represents the maximum amount of gain anticipated if the amount of resources being saved were to be reallocated to another purpose. Discussion groups with clinicians and project investigators initially determined that the non-inferiority margin should be 0.8 multiplied by the standard deviation of the targeted outcome. This is equivalent to 'Cohen's large effect size' [35]. However, review of the standard deviations for the outcomes that these stopping rules would be applied to revealed that these margins were too wide to be acceptable to the management of participating hospitals. As a result of these consultations, the following stopping rules were developed:

1. The 95% CI of the effect (difference between means) of having no weekend allied health services exceeding a 1-day increase in mean length of stay.
2. The 95% CI of the effect (difference between proportions) of having no weekend allied health services exceeding an absolute change of 0.02 (2%) in the outcomes of the proportion of patients who stay longer than their average inlier Australian Refined Diagnosis-Related Group (ARD-RG), the proportion of patients who experience one or more of the previously specified adverse events, or the proportion of patients who are unexpectedly readmitted within 28 days.

Management at each site also reserved the right to review other study data (for example, the proportion of patients discharged on the weekend) in determining whether the study should continue at each site. Interim analysis will be conducted during each month of study 1 and reported back to the project executive committee.

The project executive committee will then forward their recommendations along with blinded data to an independent data-monitoring committee at each site to make a determination as to whether the project should be ceased on the basis of the analysis conducted.

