### Data analysis

#### Sample size estimation

The sample size in this study is governed by the patient throughput on the participating wards over the trial

period. Non-inferiority trials do not preclude testing of superiority and can be done so without statistical penalty [36]; hence, we undertook power calculations for studies 1 and 2 from a superiority analysis perspective. Current data from study wards indicates there will be 7,308 patient admissions in total per study per site. We used the approach for conducting power analyses for stepped wedge trials advocated by Hussey and Hughes [37] based upon the Wald statistic. We applied this approach to 3 of our primary outcomes and demonstrated > 90% power in each case for study 1 and study 2 (Table 3). We reiterate that the actual sample size to be used in the trial has been determined primarily by practical considerations, particularly the availability of suitable wards at the participating sites.

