### Statistical analysis

**Study 1** Both non-inferiority and superiority analyses will be conducted. For non-inferiority analyses, if the non-inferiority null hypothesis is to be rejected, the upper limit of the CI around the observed difference should be less than the non-inferiority margin. Multi-level, mixed-effects generalised linear model analyses will be used to construct the 95% CIs that compare effectiveness and safety outcomes between groups. These models will nest patient admissions within wards, treating both as random factors, to account for the clustered nature of these data. Weekend allied health service delivery model provided will be treated as a fixed factor. The distribution of the length of stay outcome will be examined ( $\pm$  transformations as indicated) as a part of model building as these data are commonly skewed. Data from

**Table 3 Outcome of power analysis for three outcomes for each study at each site (assuming six wards per site), and for both sites combined**

| Outcome                                                                                | Proportion 1
(weekend allied
health services) a | Proportion 2
(no weekend allied
health services) | Single site
or both
sites combined | Assumed
coefficient
of variation | Assumed
number of
patients per
study | Power |
|----------------------------------------------------------------------------------------|------------------------------------------------------------------|--------------------------------------------------------|------------------------------------------|----------------------------------------|-----------------------------------------------|-------|
| Proportion of patients who stay longer than their AR-DRG average inlier length of stay | 0.40                                                             | 0.42                                                   | Single                                   | 0.4                                    | n = 7,000 b                        | 0.65  |
| Proportion of patients who are readmitted within 28 days                               | 0.10                                                             | 0.12                                                   | Single                                   | 0.4                                    | n = 7,000 b                        | 0.96  |

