| Proportion of patients who experience at least one of the adverse events listed        | 0.10                                                             | 0.12                                                   | Single                                   | 0.4                                    | n = 7,000 b                        | 0.96  |
| Proportion of patients who stay longer than their AR-DRG average inlier length of stay | 0.40                                                             | 0.42                                                   | Both                                     | 0.4                                    | n = 14,000 b                       | 0.99  |
| Proportion of patients who are readmitted within 28 days                               | 0.10                                                             | 0.12                                                   | Both                                     | 0.4                                    | n = 14,000 b                       | >0.99 |
| Proportion of patients who experience at least one of the adverse events listed        | 0.10                                                             | 0.12                                                   | Both                                     | 0.4                                    | n = 14,000 b                       | >0.99 |

AR-DRG, Australian Refined Diagnosis-Related Group.

aBaseline proportions based on data drawn from administrative datasets at participating sites covering a 12-month period.

bNote that for the single site analyses we assume there will be 7,308 per study, but use only 7,000 in the power analysis to allow for loss of patients during the transition phases between intervention and control conditions and for transfers between study wards. Correspondingly, we use 14,000 when considering the power of both sites combined.

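### Primary outcome 3 is defined as adverse events per person-time, but its only margin and its power calculation are for the proportion of patients with an event, so the study 1 non-inferiority test has no margin for it

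*Protocol*

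**What the plan says.** The section on primary outcome 3 lists the component events and then fixes the measure: "Rate of adverse events (events per person-time) will be considered as a single, composite end-point when considered as a primary outcome".

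Under Trial safety, the second stopping rule concerns the confidence interval for a difference between proportions "exceeding an absolute change of 0.02 (2%) in the outcomes". One of those outcomes is "the proportion of patients who experience one or more of the previously specified adverse events". The same section ties the interim checks to non-inferiority: "interim analyses will be conducted monthly to ensure that patient outcomes have not dropped below a pre-specified non-inferiority margin". A candidate margin of 0.8 standard deviations was dropped there because hospital management found it too wide.

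The Statistical analysis section plans a final non-inferiority analysis for study 1, in which "the upper limit of the CI around the observed difference should be less than the non-inferiority margin". It gives no margin of its own.

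Under Sample size estimation the protocol states: "We applied this approach to 3 of our primary outcomes and demonstrated > 90% power in each case for study 1 and study 2". The adverse-event rows of Table 3 are headed "Proportion of patients who experience at least one of the adverse events listed" and use 0.10 with weekend services against 0.12 without.

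**The concern.** One primary outcome carries two measures. They differ in the numerator, because a rate can count repeat events in one stay and a proportion cannot. They also differ in the denominator, which is time in one case and patients in the other. An absolute difference of 0.02 between proportions is not a limit on a difference or ratio of rates.

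The trial withdraws a service, and this is its primary safety outcome. With two definitions and no rule on which governs, the measure behind the final non-inferiority statement could be chosen after the results are seen. The two measures can also disagree, because length of stay drives person-time and is itself a primary outcome.

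**Working it through.** **1. Is there a margin for the rate?** Setting the passages side by side:

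- Primary outcome 3: events per person-time, composite.
- Trial safety, rule 2: proportion with one or more events, limit 0.02 absolute.
- Table 3: proportion with at least one event, 0.10 against 0.12.
- Statistical analysis: upper confidence limit to lie below the margin, no value given.

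The introduction to Outcome measures says that one primary domain gets two analyses and another is a composite. The length-of-stay section shows that the first is length of stay (the mean, and the proportion exceeding the diagnosis-group average). Adverse events are the composite. The text therefore does not provide for a second primary measure of adverse events.

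The 0.02 cannot be carried over to the rate without figures that the protocol does not give. With one event per affected patient and unchanged mean stay L, it corresponds to 0.02/L per bed-day. That is 5.0, 4.0, 3.3 or 2.5 events per 1,000 bed-days for L = 4, 5, 6 or 8. L is an assumption throughout, since the protocol states no mean stay.

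**2. Is there a power calculation for the rate?** The plan's figure for the adverse-event proportion at one site is 0.96. I checked it with the Hussey and Hughes variance:

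- Inputs: I = 6 wards, T = 7 months, 7,000/42 = 166.7 patients per ward-month, coefficient of variation 0.4, two-sided 0.05 (assumed).
- σ² = 0.11 × 0.89/166.7 = 0.000587; τ² = (0.4 × 0.10)² = 0.0016.
- One ward switches per step, so U = 21 and W = V = 91.
- Variance = Iσ²(σ² + Tτ²) / [(IU − W)σ² + (U² + ITU − TW − IV)τ²] = 0.0000415/0.2446 = 0.00017, so SE = 0.0130.
- Power = Φ(0.02/0.0130 − 1.96) = 0.34.

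The stated 0.96 does not reproduce. It appears (0.959) only with 1,000 patients per ward-month. That is a separate matter and adds nothing to this point. What matters here is that every row of Table 3 is a proportion. The protocol gives no baseline event rate, person-time or overdispersion, so power for the rate cannot be computed from it.

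**3. How far can the two measures diverge?** Assume person-time is inpatient days, one event per affected patient, and a rise from 10% to 12% (the full 0.02). Let mean stay also rise by 1 day, which is the length-of-stay limit ("exceeding a 1-day increase in mean length of stay").

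Rate ratio = (0.12/(L + 1)) / (0.10/L) = 1.2 × L/(L + 1). The extra stay that cancels the rise is 0.2 × L.

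| Assumed L (days) | Events per 1,000 bed-days: 10%, stay L | 12%, stay L + 1 | Rate ratio | Extra stay that cancels (days) |
|---|---|---|---|---|
| 4 | 25.0 | 24.0 | 0.96 | 0.8 |
| 5 | 20.0 | 20.0 | 1.00 | 1.0 |
| 6 | 16.7 | 17.1 | 1.03 | 1.2 |
| 8 | 12.5 | 13.3 | 1.07 | 1.6 |

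With stay unchanged the ratio is 1.20 at every L. With a half-day rise, 1.2 × L/(L + 0.5) gives 1.07, 1.09, 1.11 and 1.13.

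**The case against.** A reader might infer that the trial could declare withdrawal safe while more patients are harmed. The documents do not support that, for four reasons.

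- **Safeguards.** A 1-day rise in stay is exactly the length-of-stay limit, and length of stay is a primary outcome. If the true effect sits at the margin, the upper 95% limit falls below it only about 2.5% of the time. The monthly study 1 checks already use the proportion and go to an independent data-monitoring committee.
- **Dilution is not concealment.** One extra day cancels a 10% to 12% rise only if mean stay is about 5 days or less. Above that the signal shrinks but remains.
- **Direction is open.** The Background describes scant and conflicting evidence on stay, including a cited study with a non-significant 0.5-day increase when the weekend service was provided. The 0.40 against 0.42 for long stay in Table 3 is a planning assumption. If withdrawal shortened stay, the rate would be inflated instead.
- **The rate is a legitimate measure.** Falls, pressure areas and thromboses can accrue on extra days. At a constant 0.02 events per day, extending stay from 5 to 6 days gives 0.10 and then 0.12 events per admission with a rate ratio of 1.00. The rate answers a question about daily risk, and the proportion one about risk per admission.

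All four stand, and they reduce the masking argument to a conditional note. It is also true that the missing margin affects one non-inferiority test in one study: study 1 also plans superiority analyses, and study 2 has no non-inferiority analysis. None of this supplies a margin or a power calculation for the rate. A later analysis plan could choose a measure, but it would have to override either the outcome definition or the stopping rule and Table 3.

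**Conclusion.** The inconsistency holds on the text alone and needs no assumption about stay. As defined, primary outcome 3 has neither a non-inferiority margin nor a power calculation, and the study 1 non-inferiority test cannot be applied to it. Superiority analyses and study 2 are untouched by the missing margin.

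The denominator effect is secondary and conditional. It requires stay to lengthen without a proportional rise in events, and its size (rate ratio 0.96 to 1.07 instead of 1.20) rests on assumed mean stays of 4 to 8 days, one event per affected patient, and bed-days as person-time. Interim safety monitoring is not defeated; the gap falls on the final adverse-event conclusion of study 1. This should be fixed, but it does not undermine the trial's safety oversight.

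**What to change.** For the non-inferiority analysis, define primary outcome 3 as the proportion of admissions with at least one listed event. This matches the limit under Trial safety and the adverse-event rows of Table 3. Report composite events per person-time as a secondary measure, so that repeat events and time at risk remain visible.

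This is a one-sentence change on the same data. Its costs are that repeat events within a stay count once, and that the proportion combines event risk with time at risk, so it can rise through longer exposure alone.

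The alternative is to keep the rate as primary and give it its own margin and power calculation. That would also restore consistency, but it needs a baseline event rate and person-time that the protocol does not state. The final measure would also still differ from the one monitored at interim.
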